## Abstract

**Background:**

The war in Syria has displaced over 6.8 million people, more than any other conflict since the Second World War. As a result, Syrian asylum seekers and refugees have experienced several life-changing events, resulting in high rates of anxiety, depression, posttraumatic stress disorder, and suicidal ideation (SI). To address the treatment gap and reduce the burden of help-seeking, a web-based intervention to reduce SI developed for general populations was culturally adapted for and with Syrian asylum seekers and refugees in the United Kingdom. The study revealed the importance of understanding their lived experience with migration and the acculturative process in providing treatment for SI. This study will now assess the feasibility and acceptability of the culturally adapted intervention for this population.

**Objective:**

The first phase of the study will include recruiting participants and delivering the web-based intervention (1) to assess the feasibility of meeting recruitment goals and recruitment rates and (2) to assess the feasibility of outcome measures. The second phase of the study will include one-to-one semistructured interviews (1) to assess the suitability of the culturally adapted intervention in terms of recruitment and adherence rates and barriers and facilitators to engagement and (2) to assess the acceptability of the intervention in terms of its cultural relevance and appropriateness.

**Methods:**

This is a protocol for a single-group, noncontrolled, mixed methods feasibility and acceptability study of a culturally adapted web-based intervention to reduce SI for Syrian asylum seekers and refugees in the United Kingdom. The study will assess the feasibility of recruitment goals, recruitment rates, adherence rates, and outcome measures using individual participant tracking forms, which will be analyzed quantitatively. The suitability and acceptability of the intervention will be assessed using one-to-one semistructured interviews with 12 participants who completed the intervention, which will be analyzed qualitatively.

**Results:**

Recruitment began in February 2024 and will run until 30 participants are recruited to the study or until the end of July 2024. Thus far, 19 participants have provided informed consent, 16 were eligible and enrolled, and 12 have completed a postintervention interview. No data have been analyzed. The study, including the write-up period, is expected to end in December 2024.

**Conclusions:**

Despite experiencing several stressors related to forced displacement and high rates of mental health issues, access to treatment is still limited for Syrian asylum seekers and refugees in the United Kingdom. To address the treatment gap and reduce the burden of help-seeking, a web-based intervention to reduce SI was culturally adapted in collaboration with Syrian asylum seekers and refugees in the United Kingdom. This study will now assess the feasibility and acceptability of the intervention and culturally appropriate recruitment strategies.

**Trial Registration:**

ISRCTN ISRCTN11417025; https://www.isrctn.com/ISRCTN11417025

**International Registered Report Identifier (IRRID):**

PRR1-10.2196/56957

## Introduction

### Background and Rationale

The Syrian conflict has sparked the largest forced displacement crisis since World War II [1]. Experiences such as bombings, shootings, torture, and involuntary conscription have forced many Syrians to leave behind their homes, jobs, businesses, and extended families to find safety in other cities or abroad [2]. While most of the 6.8 million Syrian refugees living abroad found refuge in neighboring countries, over 1 million have sought asylum in Europe [3]. In the United Kingdom, over 20,000 Syrians were resettled under the Vulnerable Persons Resettlement Scheme [4]. Many more Syrians have sought asylum in the United Kingdom, including 75,615 applications during the year ending in September 2021 [3]. Despite having escaped war, Syrian asylum seekers continue to experience stressors while living in the United Kingdom including, most significantly, a prolonged asylum process [2]. These stressors have resulted in elevated rates of mental health issues including major depressive disorder, posttraumatic stress disorder (PTSD), and suicidality [5]. There is thus an urgent need to improve the understanding and care of mental health issues for Syrian asylum seekers and refugees arriving in the United Kingdom.

### Suicidal Ideation

One of the most concerning and least addressed mental health issues for asylum seekers and refugees across Europe is suicidal ideation (SI) and suicidal behavior more broadly [6]. Several studies have shown high rates of SI among asylum seekers and refugees in Sweden, 33.9% [7] and 48% [8]; Switzerland, 42.1% [9] and >30% [10]; and the United Kingdom, 40.9% [11]. Some studies, however, have shown lower rates of suicide attempts among refugees than the Swedish-born population, suggesting variances between asylum seekers and refugees [12]. In fact, a study in Switzerland found that the most frequent reason for referral to emergency psychiatric services among asylum seekers was SI after the rejection of their asylum application [9]. Studies on Bhutanese refugees in the United States have also showed lower rates of SI at 3% [13], 6.2% [14], and 6.7% [15]. However, Meyerhoff and Rohan [15] found a large disparity between their reports of SI, 6.7%, and desire for death, 48.3%, suggesting that culturally inflexible models could mask the real prevalence of SI for different asylum seeker and refugee subgroups. Most importantly, despite their risk for developing mental health issues and SI, refugees and asylum seekers continue to underuse mental health services [16-19].

### Cultural Adaptation

Access to treatment for SI among Syrian asylum seekers and refugees in the United Kingdom can be improved with culturally adapted digital mental health interventions [20]. In response to the treatment gap, Beuthin et al [21] culturally adapted a digital intervention to reduce SI with and for Syrian asylum seekers and refugees in the United Kingdom. The study built on Eylem and colleagues’ [22] cultural adaptation of van Spijker and colleagues’ [23] Leven onder Controle (literally “Living under Control”) intervention, a guided 6-week cognitive behavioral therapy–based web-based intervention to reduce SI. The intervention includes 6 modules: thinking about suicide, dealing with thoughts and feelings, thinking about the future, thinking about the self, thinking about others, and repetition and relapse. Several randomized controlled trials (RCTs) have found the intervention to be effective in reducing SI compared to treatment as usual—an information website—for general Dutch (*d*=0.2) [24] and Belgian populations (*d*=0.34) [25] but not for Australian populations [26]. The initial cultural adaptation of the intervention for Turkish immigrants in the United Kingdom and the Netherlands was found to be acceptable; however, the study was unable to recruit enough participants for a full RCT [22].

Eylem et al [22] culturally adapted the intervention in line with Bernal and colleagues’ [27] framework, which included adapting for cultural metaphors, treatment concepts and goals and the context and methods of the intervention. This framework falls within the school of thought which, based on the universality of emotional expression, asserts that the distinct signs and symptoms of psychopathology are universal. It therefore aims to maintain the integrity of the original intervention as much as possible. However, cultural adaptation based on universal signs and symptoms undermines the more fundamental role of intentions and conventions in meaning making [28]. Conversely, another framework developed by Horrell [29] aims to develop new interventions for different cultural groups. While it is certainly more situated, the framework does not consider the role of acculturation and cultural change. Beuthin et al [21] therefore synthesized these approaches by focusing on shared lived experiences that give rise to (1) core affect, including hedonic valence and physical arousal; and (2) conceptual knowledge [30]. In other words, feeling is perceiving, and perceiving is believing and vice versa [31]. This framework therefore enables researchers to identify resilient core beliefs, which in turn are important in understanding and avoiding identity crises [32] and suicidal behavior [33]. With this paradigm in mind, the cultural adaptation process was simplified using experience-based co-design, an action research method for collaboratively improving health care services and interventions [34]. This entailed interviews to understand Syrian asylum seekers’ and refugees’ cultural conceptualizations, coping-strategies, and help-seeking behavior for mental health and SI in relation to touchpoints, crucial moments that made a difference in their experience, of the migratory process [2]. After a preliminary cultural adaptation of the intervention, Syrian asylum seekers and refugees participated in co-design events to collectively identify and adapt touchpoints of the intervention. A community research panel also helped to maintain the integrity of the intervention and the users’ core beliefs at each phase of the cultural adaptation. Importantly, intentions and conventions are not understood as a spectrum, but rather, all communication by definition is intentional but differs in the level to which it adheres to conventions.

Based on the findings of Beuthin et al [2], the main cultural adaptations to the intervention included case examples, coping strategies, and a nondirective approach. Case examples included a wish for death during the post-migration phase, and SI crises during the pre- and peri-migration phases. Notably, a participant who experienced an SI crisis described his thoughts as both SI and a wish for death, potentially highlighting a more salient mechanism of SI for this population. However, while attributing their thoughts to their experiences, they believed that suicide is fundamentally a consequence of diminished sources of support including weak imān (faith), a loss of one’s mind, character and soul, and a lack of access to mental health support. Similarly, participants identified their coping strategies as conceptualizing their experiences as ibtilā’ (a test) and being hopeful of God’s help while engaging in acts of worship, hobbies, walking, volunteering, talking to family and friends, etc. In contrast to the previous feasibility study by Eylem et al [22] that suggested the intervention should be shortened, participants preferred maintaining the integrity of the intervention while providing more explanations about their purpose [2]. Participants were also directly involved in the cultural adaptation process through 3 co-design events, which involved adapting 2 sessions of the intervention each. However, since participants did not use the intervention, this study will now assess its acceptability and suitability by providing it in full to Syrian asylum seekers and refugees in the United Kingdom with SI.

### Recruitment

In addition to the cultural adaptation of the intervention, Eylem et al [22] expressed the need to identify culturally appropriate recruitment strategies. Despite advertising their study through public events, newspaper advertisements, television programs, banners on websites, and social media, they were unable to recruit enough participants for a full RCT. They believed that recruitment was hindered by institutional barriers for different Turkish subgroups and therefore recommended task-shifting recruitment to trained lay people from the target population. This was confirmed in a previous study by Beuthin et al [2], which recruited all its participants through cultural brokers via the web. Most charities and nongovernmental organizations (NGOs) contacted in the previous study reported having insufficient capacity to disseminate the study advert. Likewise, participants of the study reported avoiding seeking help via the National Health Service (NHS) due to the long waiting times and fear of having their asylum application rejected. Several Syrian mental health researchers in the United Kingdom confirmed that despite holding events and advertising through mosques, charities, and NGOs, they too only received responses via advertisements in Syrian diaspora Facebook groups. Thus, this study will assess the feasibility of recruiting Syrian asylum seekers and refugees in the United Kingdom with SI from various sources including charities, NGOs, local councils, social media, but most importantly, cultural brokers.

### Aims

This study is part of a broader research project aimed at improving the understanding and treatment of SI among Syrian asylum seekers and refugees arriving in the United Kingdom. The study aims to investigate the feasibility and acceptability of a culturally adapted web-based stand-alone intervention to reduce SI for Syrian asylum seekers and refugees in the United Kingdom.

### Objectives

The first phase of the study will include recruiting participants and delivering the digital intervention (1) to assess the feasibility of meeting recruitment goals and recruitment rates and (2) to assess the feasibility of outcome measures. The second phase of the study will include one-to-one semistructured interviews (1) to assess the suitability of the culturally adapted intervention in terms of recruitment and adherence rates as well as barriers and facilitators to engagement and (2) to assess the acceptability of the culturally adapted intervention in terms of its cultural relevance and appropriateness and whether participants were satisfied with their experience.

## Methods

### Study Design

This is a single-group, noncontrolled, mixed methods feasibility and acceptability study of a culturally adapted web-based intervention to reduce SI for Syrian asylum seekers and refugees in the United Kingdom. The feasibility and acceptability study will follow the SPIRIT (Standard Protocol Items: Recommendations for Interventional Trials) 2013 Guidance for protocols of clinical trials [35] and the CONSORT (Consolidated Standards of Reporting Trials) 2010 extension for randomized pilot and feasibility trials [36].

Expanding on the feasibility study by Eylem et al [22] of the same intervention, the study will assess the feasibility of recruitment methods in meeting recruitment goals. Previously, Eylem et al [22] aimed to conduct a full RCT; however, they were unable to meet their recruitment goal of 286 participants, recruiting instead 85 participants, 30 of whom were found to be eligible, and only 18 provided consent. They therefore recommended task-shifting to trained lay people or cultural brokers to overcome institutional barriers to recruitment.

The feasibility of recruitment goals and recruitment rates will be assessed in accordance with the guidelines for evaluating the feasibility of recruitment in pilot studies of diverse populations developed by Stewart et al [37]. Their guidelines include the following eight steps: (1) specifying recruitment goals (target population, desired diversity, and subgroup sample sizes), (2) specifying recruitment processes by stage, (3) establishing a tracking system for each individual (contact tracking form), (4) establishing a tracking database for monitoring processes and results, (5) implementing recruitment processes and monitoring each individual’s progress, (6) summarizing recruitment results from the tracking database, (7) calculating and interpreting measures of feasibility, and (8) modifying methods for a larger study if recruitment goals are not met. Their guidelines will be described in more detail in the Data Collection, Management, and Analysis section.

Like the feasibility study by Eylem et al [22], one-to-one semistructured interviews will be conducted with intervention participants to understand the suitability and acceptability of the culturally adapted intervention. This will include identifying the barriers and facilitators to engagement and the cultural appropriateness and relevance of the culturally adapted intervention. Like the initial cultural adaptation process for Syrian asylum seekers and refugees in the United Kingdom, the interviews will involve asking participants to identify touchpoints of the intervention [34]. Research methods will be described in more detail in the Data Collection, Management, and Analysis section.

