##### Secondary Outcomes

Secondary outcomes include the feasibility of recruitment goals and measurement instruments. Recruitment goals will be tracked in accordance with the guidelines by Stewart et al [37] for diverse populations. This will include using an eCTF to track the sources of potential participants (NGOs, charities, and social media), the number of participants recruited within the set time period (30 in 6 months), sample characteristics (age, gender, ethnicity, and religion), and reasons for loss at each stage (consent, eligibility, enrollment, etc).

The feasibility of measurement instruments will be assessed in terms of the number of people who completed questionnaires, the amount of information missing, which should not exceed 10%, and the time it took to complete them. This will include measuring SI for intervention participants at baseline (T1), after 3 weeks (T2), and post treatment (6 weeks after baseline: T3). Depression, anxiety, and PTSD will also be measured at baseline and post treatment. If possible, all participants who begin the intervention will complete the follow-up assessment at week 6 irrespective of whether they complete the intervention or not. All the data will be recorded on the eCTF. The outcome measures used in the study are as follows:

SI will be measured using the SI subscale of the C-SSRS, which is a 6-item tool used to assess SI [38], which has shown good internal consistency (α=.966) for an Arabic-speaking population [39]. The C-SSRS was chosen due to its compatibility with Syrian’s conceptualization of SI as a wish for death. An answer of yes to any of the 6 questions indicates a presence of SI, and a score of 4 and above indicates serious SI.

Anxiety and depression will be measured with the Hospital Anxiety and Depression Scale (HADS) [40,41]. The Arabic version has shown acceptable internal consistency for both the anxiety (α=.73) and depression scale (α=.77) [42]. HADS consists of 14 items, which are scored on a 4-point Likert scale between 0 and 3. The total score range is between 0 and 21, with scores between 0 to 7 indicating normal anxiety or depression, scores between 8 to 10 indicating borderline abnormal anxiety or depression, and scores above 11 indicating abnormal anxiety or depression.

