### Sample Size

The study aims to recruit 30 male or female Syrian asylum seekers and refugees in the United Kingdom, aged 18 years and older, with at least a score of 1 on the C-SSRS [38]. To assess the acceptability of the intervention, at least 12 eligible participants must be recruited for the intervention and postintervention interviews within 6 months (February to July 2024). This number was chosen to enable data saturation for the acceptability and suitability interview at 7 participants while compensating for expected attrition. Since the target population are minorities in the United Kingdom, recruitment is expected to have a lower yield within the allocated time period. If possible, participants will be stratified for sex (male: n=6 and female: n=6), major ethnic groups (Arab: n=10 and Kurdish: n=2), and age (18-39 years: n=10 and 40 years and older: n=2). The National Center for Complementary and Integrative Health notes that sample sizes should be based on practical considerations, including participant flow, financial constraints, and the number of participants needed to evaluate feasibility goals [44]. For qualitative work, 30 or less participants are enough to reach saturation.

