### Recruitment

As mentioned before, Eylem et al [22] were unable to recruit enough participants for an RCT and therefore recommended task-shifting to lay people associated with the target population. Task-shifting recruitment to community-based health workers and volunteers has shown to improve recruitment and access for minority ethnic groups [45,46] and was also suggested to scale up mental health interventions for Syrian refugees in the Middle East and Europe [47]. Thus, participants will be recruited via cultural brokers as well as NGOs, charities, local councils, and social media.

The study will use purposive sampling to recruit participants from various demographic backgrounds including age, gender, religion, ethnicity, and refugee status. All recruitment will be via the web using a study advertisement or email correspondence, which will outline the purpose and development of the intervention. OB will be responsible for all direct communication with participants and external individuals and organizations involved in sharing information about the study. The recruitment process will be recorded using an eCTF in accordance with the 8-step guidelines of Stewart et al [37], which includes tracking the sources of potential participants (NGOs, charities, local councils, and social media), the number of participants recruited within the set time period (60 in 6 months), sample characteristics (age, gender, ethnicity, and religion), and reasons for loss at each stage (consent, eligibility, randomization, waiting list, intervention, and interview). No incentives for participation will be provided other than access to the intervention.

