## Results

Recruitment began in February 2024 and will run until 30 participants have been recruited to the study or until the end of July 2024. Thus far, 19 participants have been recruited and provided consent, 16 of whom were eligible, and 12 have completed the postintervention interview. All but one participant were recruited via cultural brokers. The study, including the write-up period, is expected to end in December 2024.

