Since the participants involved in the cultural adaptation process did not use the intervention and some did not have SI, further research is needed to assess its feasibility and acceptability to users with SI. Thus, this study will consist of two phases: (1) recruiting participants and delivering the digital intervention and (2) one-to-one semistructured interviews. First, participants will be recruited from various sources including cultural brokers via the web, NGOs, and charities to assess the feasibility of meeting recruitment goals and recruitment rates. Second, interviews will be conducted to assess the suitability and acceptability of the culturally adapted intervention. Findings from the study could result in further adaptations to the intervention including those already made as well as inform the design of a future RCT. Two areas that are most likely to require further adaptation are the Arabic translation and content on SI. As English and Arabic belong to very distant language families, it can be challenging to translate in either direction. Likewise, the extent to which Syrian asylum seekers and refugees are willing to approach their thoughts about suicide directly is still unknown. The findings of the study may also indicate the need to reduce the number of outcome measures or questions to be asked in a future RCT as well as the amount of contact with researchers.

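### The goal of 30 participants in 6 months is not tied to any rate a future RCT would need, so meeting it does not by itself show that RCT recruitment is feasible

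*Protocol article*

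**What the plan says.** All references are to the protocol article.

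- **The trigger.** Study Design lists the eight steps of the guideline it will follow. Step 8 is "modifying methods for a larger study if recruitment goals are not met". Step 1 shows that goals are wider than a head count: "specifying recruitment goals (target population, desired diversity, and subgroup sample sizes".
- **The time-based goal.** Secondary Outcomes gives "the number of participants recruited within the set time period (30 in 6 months"). The Abstract, Sample Size and Results also give 30. The Recruitment section under Methods gives "the number of participants recruited within the set time period (60 in 6 months").
- **When recruitment ends.** Under Results, recruitment "will run until 30 participants have been recruited to the study or until the end of July 2024".
- **Where the numbers come from.** Sample Size justifies a minimum of 12 by interview saturation and expected attrition. It refers to practical considerations and the sufficiency of 30 or fewer for qualitative work. It also says: "Since the target population are minorities in the United Kingdom, recruitment is expected to have a lower yield within the allocated time period".
- **The recruitment problem behind the study.** Of the earlier trial of the same intervention, Study Design says "they were unable to meet their recruitment goal of 286 participants". That trial recruited 85, of whom 30 were eligible and 18 consented.
- **Intended use.** Expected Findings says the results could "inform the design of a future RCT".
- **What will be reported.** Quantitative Outcomes lists percentages by recruitment stage and by source, the number recruited in the period, and sample characteristics. Primary Outcomes sets a 70% criterion at each recruitment stage.

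**The concern.** The article repeatedly presents recruitment as the obstacle that stopped the earlier RCT, and step 8 is explicitly about a larger study. A goal used in that step should therefore say something about whether a larger study could fill. The goal of 30 in 6 months is not linked to an RCT size, an RCT duration or a required monthly rate.

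The stopping rule adds to this. Because recruitment closes at 30, every successful outcome yields the same count. A study that reaches 30 in ten weeks and one that reaches it on the last day both report 30 within the period, and neither time to 30 nor enrolment per month is listed as an output.

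At stake is what the result can be used for. Meeting the goal could be read as support for carrying the same recruitment methods forward, at a rate that might be too slow for the trial it is meant to inform.

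**Working it through.** **Inputs from the article.** Goal 30 in 6 months (Secondary Outcomes; 60 in Recruitment under Methods). Earlier trial's target 286 (Study Design). Published effects of the intervention d = 0.34 and d = 0.2 (Cultural Adaptation). Recruitment stops at 30 (Results).

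**Assumptions, not in the article.** A constant recruitment rate with Poisson counts; 286 as an illustrative RCT size; for the other sizes, a two-arm comparison of means with 80% power, two-sided 5%, 1:1 allocation and no attrition. The goal of 30 has no formula behind it, and the inputs to 286 are not given, so neither figure can be reproduced.

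**1. Rate at a bare pass.** 30/6 = 5 per month. Time to 286 = 286/5 = 57.2 months (4.8 years). With a goal of 60: 60/6 = 10 per month, and 286/10 = 28.6 months.

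**2. Uncertainty if exactly 30 are enrolled over the full 6 months.** Exact Poisson 95% limits for a count of 30: lower = χ²(0.025; 60 df)/2 = 20.2, upper = χ²(0.975; 62 df)/2 = 42.8. Divided by 6, this is 3.37 to 7.14 per month. Time to 286 is then 286/7.14 = 40 months to 286/3.37 = 85 months.

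**3. Chance of meeting the goal at different true rates.** P(Poisson(6r) ≥ 30):

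| True rate r per month | P(at least 30 in 6 months) | Months to 286 |
|---|---|---|
| 5 | 0.52 | 57.2 |
| 6 | 0.86 | 47.7 |
| 7 | 0.98 | 40.9 |

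The goal is thus likely to be met at rates that imply more than three years for 286. For scale, filling 286 in 24 months (an assumed window) needs 286/24 = 11.9 per month, 2.4 times the goal rate.

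**4. What the stopping rule hides.** If 30 is reached in m months, the time to 286 is 286 × m/30:

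| Months to reach 30 | Months to 286 | Count reported |
|---|---|---|
| 2.5 | 23.8 | 30 |
| 3 | 28.6 | 30 |
| 4 | 38.1 | 30 |
| 5 | 47.7 | 30 |
| 6 | 57.2 | 30 |

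The reported count is the same in every row.

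**5. Does this depend on 286?** A two-sample t-test needs 137 per arm (274) for d = 0.34 and 394 per arm (788) for d = 0.2. At 5 per month these take 274/5 = 54.8 and 788/5 = 157.6 months. The absence of a link between the goal and an RCT's needs does not rest on 286.

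**6. Do the other criteria fill the gap?** The 70% criteria are proportions between stages, and the diversity and subgroup goals concern composition. All can be met at any speed. The only planned measure that involves time is the count within the period.

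**The case against.** The strongest reply is that the article never claims that reaching 30 proves an RCT feasible. Its aims are the feasibility and acceptability of the intervention, the number recruited is a secondary outcome reported descriptively, and the findings are only said to be able to inform a later design. This stands, and it limits the point to what a pass can and cannot show.

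A reader might infer that methods will change only if 30 is missed, so that step 8 has a single input. The text does not support that. It has no such restriction, it speaks of goals in the plural, step 1 includes diversity and subgroup sizes, step 7 interprets feasibility measures first, and the 70% criteria exist as well.

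A reader might also infer that a pass means repeating the same methods and the same shortfall. The article does not support that either. Limitations already considers NHS recruitment for a future RCT, and the earlier trial's recruitment period is not given, so the two rates cannot be compared.

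Further, 286 was set for Turkish immigrants in two countries and is not this programme's RCT size. Straight-line projection from a study in which one researcher handles all direct contact with participants is rough. Both are fair, and they are reasons to show a range. They do not supply the missing link between the goal and an RCT's needs.

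Finally, a monthly rate can be derived from the enrolment dates, and an interval is a detail that a condensed article may leave out. But the article does state the goal, the measure and the stopping rule, and together these make the stated measure uninformative about speed once 30 is reached.

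**Conclusion.** The point holds in limited form. The time-based goal is not derived from a rate that a future RCT would need, yet step 8 links changes of method for a larger study to whether recruitment goals are met. At a bare pass the illustrative 286 would take about 57 months (95% interval about 40 to 85), or 28.6 months if the goal is 60. Because recruitment stops at 30, the count alone cannot distinguish these rates from faster ones.

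It would go too far to say that a pass cannot inform RCT feasibility, or that it commits the team to four to five years. The 57 months apply only to a pass at the very end of the period, and the time taken to reach 30 is informative if it is reported. Whether 57 months is too long is a judgement, since the article sets no RCT size or window. The projections assume a constant rate and Poisson counts, and those for 274 and 788 also assume 80% power, two-sided 5% and no attrition.

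**What to change.** 1. Reconcile 30 and 60 in 6 months between Secondary Outcomes and the Recruitment section under Methods.
2. In Secondary Outcomes and Quantitative Outcomes, add enrolment per month: number enrolled divided by months open, including when 30 is reached early, with an exact Poisson 95% interval. If recruitment closes on reaching 30, the upper limit should use 60 rather than 62 degrees of freedom, because time and not the count is then random (41.6 instead of 42.8; little changes).
3. Report the projected months to a range of RCT sizes, for example 286, or about 274 to 788 from the published effects, with assumptions stated.
4. In Study Design, say that step 8 will weigh this projection alongside the diversity, subgroup and 70% stage criteria, and that meeting the count alone will not be taken as evidence that the methods suffice for a larger study. A fixed cut-off on projected time cannot be applied until an RCT size and window are set.

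The cost is one calculation from enrolment dates and a few sentences. The sample size and conduct of the study do not change. The downside is that a study that meets its goal may still have to report that recruitment is too slow for an RCT.
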